## 2. Methods

### 2.1. Study Design

The PACO study is a randomized controlled trial setting in public high schools from three Spanish cities (Granada, Jaén, and Valencia), where the schools are the units of randomization, and individuals within the schools are the units of analysis (the participants). The intervention focuses on promoting cycling to school and will be implemented in adolescents during 1 month within the physical education (PE) curriculum classes. Six high schools (i.e., an intervention and a control school in each of the 3 involved cities) will be randomly selected to participate. All study participants will be assessed before and after the intervention period using assessment procedures described below.

The PACO study has been approved by the Review Committee for Research Involving Human Subjects at the University of Granada (Reference: 162/CEIH/2016) and registered with a ClinicalTrials.gov ID: NCT03937336. In addition, the present study protocol has been written in accordance with the Standard Protocol Items: Recommendations for Interventional Trials (SPIRIT) statement (see supplementary file 1).

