### 2.2. Study Population

A total of 360 adolescents aged 14–15 years (3rd grade of secondary education; hereinafter called 3rd grade) from 6 high schools located in 3 Spanish cities will be recruited (see Figure 2). The randomization process is presented in the Figure 2. Within each city, 2 high schools, randomly selected and allocated to intervention or control treatment, will participate in the study. Within each secondary school, two class groups of approximately 30 participants each will be invited to participate and allocated to intervention or control conditions. The final target sample will comprise 360 adolescents (120 adolescents per city; 180 adolescents in the intervention and 180 in the control group).

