The perceived barriers to allow their children to commute actively to school will be assessed using the previous valid and reliable PABACS (Parental Perception of Barriers towards Active Commuting to School) questionnaire in Spanish children and adolescents [68]. It is a 23-item questionnaire categorized into 3 scales (general, walking, and cycling barriers) designed to determine the main parental barriers. The final variable to analyse will be an average score ranging from 1 to 4 (strongly disagree to strongly agree), for every item and for every scale.

(8) Peer social support

The peer social support to ACS will be self-reported by parents using a question from the School Travel and Safety survey used in the “Walk to School” study among American children [5]. The question will be: *“How often do other people in the neighbourhood walk or cycling with children to/from school?”* Response options: *everyday, a few times a week, a few times a month, a few times a year, or never*. The final variable to analyse will be the percentage of parents at a given school who will respond “everyday” or “a few times a week”.

(9) School characteristics

The student enrolment will be a measure of the school size (i.e., the number of students enrolled in the school during the year of participating in the current study). The school socioeconomic status will be calculated in accordance to previous studies [77,78]. Then, school neighbourhoods will be objectively analysed and classified as high or low socioeconomic status based on a Geographic Information System. The school engagement (to define its implication within the study since it might influence the intervention effects obtained in the study) will be 3 study reporting 3 variables per school: “teacher’s engagement” (i.e., the average of the researcher staff perceptions of the teacher’s engagement from all the classes); “student’s engagement” (i.e., the average of the researcher staff perceptions of the student’s engagement from all the classes); and “school’s engagement” (i.e., the average of the previous teachers and student’s engagement).

(10) City characteristics

The population density (number of inhabitants per city area in km^2^ -inhabitants/km^2^-) will be obtained from the Ministry of Finance and Public Administration of Spain, using the available data closest to the data collection year in each city. The city income from the data collection year will be obtained from the Spanish Public Tax Agency.

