The following covariables will be included in the regression models: children´s age and gender, date of birth, school grade and name, class, bicycle ownership, parent´s age and gender, weight, height, waist circumference, body mass index, family income, parental educational level, student enrolment, school socioeconomic status, school engagement, population density, city income, distance home-school, cycling lane length, bicycle racks and weather.

Considering that our main aim is to assess real-world effectiveness of the intervention, we will conduct a primary analysis based on an intention-to-treat principle (in which we will analyse participants according to the groups originally assigned). Then, we will conduct a sensitivity analysis per protocol (in which we will exclude participants who did not complete the intervention and/or did not reach a minimum of 75% of attendance).

Analyses will be conducted using the Statistical Package for Social Sciences (SPSS, v. 25.0, IBM SPSS Statistics, IBM Corporation), and the level of significance will be set at *p* < 0.05.

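### The covariate list for the change-score regressions includes school name and class, which determine study group, so the group coefficient in those regressions is not estimable

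*Protocol article*

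**What the plan says.** Section 2.1 describes a design "where the schools are the units of randomization, and individuals within the schools are the units of analysis", with "an intervention and a control school in each of the 3 involved cities". Section 2.2 gives the target as "120 adolescents per city; 180 adolescents in the intervention and 180 in the control group".

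Section 6 first assigns the main effects of study group to an ANCOVA. It then adds regression models for the change from baseline to post-intervention, with study group as a fixed factor. A list of covariables follows, which it says will be included in the regression models. Among them are "date of birth, school grade and name, class, bicycle ownership" and "student enrolment, school socioeconomic status, school engagement, population density, city income, distance home-school, cycling lane length, bicycle racks and weather". The section gives no selection rule, random effect or reduced model for these terms.

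Section 4.2.2 explains why school engagement is recorded: "since it might influence the intervention effects obtained in the study". It is an average of the research staff's perceptions of teacher and student engagement.

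**The concern.** If every pupil in a school is in the same arm, knowing the school means knowing the arm. A model that contains both study group and school name as fixed terms has no separate information with which to estimate the group effect. The same is true of class, and six schools offer very little between-school information for the other contextual variables to share.

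Software does not usually stop at this point. It drops or zeroes a redundant term. The figure reported as the intervention effect would then be missing, or would depend on coding or order of entry. These regressions cover the primary outcomes (cycling to school, active commuting and physical activity).

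School engagement raises a different problem. It describes involvement in the study and so probably arises after allocation. Adjusting for a variable that allocation may have changed can bias the effect even where the model is estimable.

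**Working it through.** **Inputs.** Six schools, one per arm in each of three cities (section 2.1). Two classes of about 30 per school, so 12 classes (section 2.2). The plan's total reproduces: 3 × 2 × 2 × 30 = 360, or 180 per arm.

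**Assumptions for the check.** Eight placeholder pupil-level covariates, and arbitrary values for the school- and city-level covariates, because the documents give no actual values. School socioeconomic status and racks were entered as binary; population density and city income varied only by city. Class means 12 distinct class groups.

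**Criterion.** The group coefficient is estimable only if deleting the group column lowers the rank of the design matrix.

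**School name, by hand.** Group equals the sum of the indicators of the three intervention schools. Intercept plus five school indicators has rank 6, and adding group leaves it at 6.

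**Room for school- and city-level terms, by hand.** Six schools allow six independent school-level columns. The intercept takes one and group takes one: 6 − 1 − 1 = 4 remain. The list has seven (enrolment, school socioeconomic status, engagement, population density, city income, lane length, racks), before weather.

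**Rank check, school allocation.** Every row contains intercept, group and the eight pupil-level columns (10 columns).

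| Added terms | Columns | Rank | Group estimable? |
|---|---|---|---|
| none | 10 | 10 | yes |
| two city indicators | 12 | 12 | yes |
| school name (5 indicators) | 15 | 14 | no |
| class (11 indicators) | 21 | 20 | no |
| seven school/city covariates | 17 | 14 | no |
| those seven plus weather | 18 | 14 | no |
| four school-level covariates | 14 | 14 | yes |
| five school-level covariates | 15 | 14 | no |
| school name, class, the seven and weather | 34 | 20 | no |

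Entering school and class as numeric codes does not help: with the seven covariates and weather, the rank is 15 in 20 columns and group is not estimable. If class is only a label such as A or B that recurs across schools, the model with school name still fails (15 in 16).

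**How far the seven-covariate result depends on the values.** Suppose school socioeconomic status and racks turn out to be the same in all six schools. The intercept and the other five covariates still fill all six dimensions unless their values coincide in a special way, so group stays aliased.

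**Alternative reading.** Section 2.2 also says that, within each school, "two class groups of approximately 30 participants each will be invited to participate and allocated to intervention or control conditions". If classes were allocated within schools, group would be estimable with school name (15 in 15) and with the seven covariates (15 in 17, where the redundancy lies among the covariates). It would still not be estimable with class (20 in 21).

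**The case against.** A reader might infer that the trial has no estimable intervention effect. The document does not support that. The ANCOVA is the first-named analysis of main effects, the change-score regression is introduced as an addition to it, and the list is attached to the regression models. The ANCOVA's own covariates are not stated, so its group effect may well be estimable.

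Section 4.2 calls the other variables potential mediators or covariates, which could mean a pool to choose from, and a statistical analysis plan may narrow it. Section 6 is firmer, however: it says the listed variables will be included. This softens the point without removing it.

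The result for the seven covariates is generic. It is what nearly any set of school values would give, but it is not shown from the actual values. The aliasing by school name needs no such assumption under school allocation. Nor does the aliasing by class when the 12 classes are identified separately.

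It is tempting to say that adjusting for engagement removes part of a real effect. The document does not say when engagement is rated, or show that the intervention changes it. Bias is possible in either direction.

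The list also has redundancies that do not alias treatment: date of birth repeats age, and school grade is constant because all pupils are in 3rd grade. Body mass index is a non-linear function of weight and height, so it is not an exact linear redundancy. None of these adds to the case.

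Finally, estimability alone does not require removing every school- and city-level variable, since up to four independent ones could stay.

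**Conclusion.** The point holds for the change-score regressions. As listed, they contain school name and class as fixed covariates beside study group, and their group coefficient is not estimable. This rests on allocation of whole schools, which section 2.1 states. Under a class-allocation reading, class alone still aliases group.

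Removing only school name and class would probably not be enough. Seven school- or city-level terms compete for four places, and weather, measured at the station nearest each school, would be an eighth if constant within school. A random school effect would remove the aliasing with school name but not this saturation.

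The conclusion does not extend to the ANCOVA. On engagement it goes no further than a probable post-allocation variable with bias of unknown direction. Because a stated model for the primary outcomes cannot deliver its treatment coefficient, the text needs correcting before analysis.

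**What to change.** - Remove school name and class as fixed covariates from any model that estimates the intervention effect. Treat school as the cluster, with a small-sample method suited to six clusters. The between-school degrees of freedom are few: 6 − 1 − 1 = 4 after intercept and group, and 4 − 2 = 2 if city is also fitted.
- Remove school engagement from effect models.
- Limit adjustment to pre-intervention pupil-level variables already on the list, plus the baseline value of the outcome and, if wanted, city as the stratum. In the check, group with pupil-level terms and two city indicators has full rank (12 in 12).
- Report the remaining school- and city-level variables descriptively by school. Keeping a few is algebraically possible, but each uses one of the few between-school degrees of freedom.
- Say whether the covariate list also applies to the ANCOVA. If it does, the same correction applies there.
- Dropping date of birth (with age retained) and the constant grade is optional tidying.

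The change is to wording only; no data collection is affected. The cost is less adjustment for school context, which six schools cannot support.

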The 7 h intervention has four sessions that will be implemented during PE sessions over a period of one month (1 weekly session). An expert teacher in cycling in an urban context will lead all the intervention sessions, and the PE teachers will attend to learn and support the sessions. The sessions are described below (see Figure 4):

(1) Theoretical session (60 min—first week): theoretical session in the classroom to provide the participants a first step in the concept of cycling as a mode of commuting in the city. The content will include: awareness about the benefits and usefulness of cycling as a mode of commuting, knowledge about road safety rules for cycling, knowledge about cycling safety equipment for both the rider and the bicycle, and cycling hand signals in urban context.

(2) Closed circuit session (120 min—second week): practical session on the school grounds to learn or improve the fundamental cycling skills needed to ride the bicycle safely. The participants will practice how to fit the helmet and check the bicycle before cycling, as well as the fundamental cycling skills through 10 activities and a cycling circuit. The contents will include: correct helmet fitting, bicycle safety check before the ride, and the fundamental cycling skills of starting off and pedalling, breaking safely, changing gears, and hand signals to change directions.

(3) Urban circuit session (120 min—third week): practical session in urban context on-road traffic to transfer the previously learnt cycling knowledge and skills. The participants will learn advanced cycling skills on-road and will use the previously learnt cycling skills in new, uncertain, and modifiable on-road situations exposed to urban traffic. The content will include: starting from side of road (curb), stopping on side of road (kerb), overtaking a parked or slower-moving vehicle, lane changing, turning right and left, and crossing a roundabout.

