#### 4.2.2. Other Variables

(1) Sociodemographic characteristics

Participants and their parents will complete questions on sociodemographic characteristics, such as age, school grade and class, gender, full postal address and children´s bicycle ownership.

(2) Cycling knowledge and skills

The knowledge about route safety rules, cycling hand signalling, and circulation will be self-reported by participants at classroom, completing a 20-questions test with multiple-choice answers [56]. A final score will be obtained with the number of correct answers.

The cycling skills of the participants will be measured during the second and third session of the school-based intervention using two ad hoc observational checklists completed by the cycling teacher after every participant´s performance indicating a dichotomic answer (*yes/no*). The observational checklist for the second session on cycling traffic-free includes 18 skills grouped in 6 categories (i.e., starting off, pedalling and changing gears; turning right; turning left; performing zig-zag; breaking; unexpected turning) and the observational checklist for the third session on cycling on-road includes 32 behaviours grouped in 7 items (i.e., starting from side of route (kerb) and starting off; overtaking and lane changing; turning left to a secondary street; turning right to a secondary street; turning left to a main street; turning right to a main street; crossing a roundabout), and both includes a final item about the participant´s general behaviour. A final score will be obtained by every participant of 0–18 points in the first checklist and 0–32 points in the second checklist. For safety reasons, the participants that will not achieve at least 10 points and six compulsory behaviours related to perform safety right and left turns in the first checklist during the traffic-free cycling lesson, will not be invited to participate in the next on-road cycling session. The checklist is also available elsewhere [56].

(3) Perceptions

Participants will complete questions about their perceived barriers to ACS using the previous valid and reliable BATACE (*BArreras en el Transporte Activo al Centro Educativo*) Scale in Spanish adolescents [64]. It is an 18-item scale related to the environment/safety and planning/psychosocial factors. The final variable to analyse will be an average score ranging from 1 to 4 (strongly disagree to strongly agree), for every item and for every factor.

(4) Psychosocial

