In the search for balance, several pragmatic adaptations will be made to conduct the research in “real-world” scenarios (such as school) where decisions need to be made on how to best conduct the study with the limited amount of time and resources that researchers may have [82]. In the PACO study, these adaptations pertain to the study design, implementation, and evaluation. Firstly, the school teachers will be able to choose the participating class groups, within the same grade. The pilot study and several consultations with school teachers showed that teachers want to choose the participating class and this will increase their involvement in the intervention. Secondly, all high schools in the three participating cities will be included in the random selection processes and then, the chosen schools will be invited to participate. Time limitations do not allow to visit each school for this purpose, and emails to schools have been previously sent (in previous studies of the research group) and they have not been answered because of high workload. Consequently, we will include all the schools in the random process to guarantee that everyone has the same likelihood to be selected. Thirdly, the intervention includes 4 sessions during a 1-month period. Research staff will offer the option to teachers of spreading the 2 h lesson of the 2nd and 4th session in two 1 h sessions using the normal PE schedule. In Spain, the national educational system in secondary schools mandates 2 h per week of PE. Fourthly, regarding the organization of the academic year in 3 trimesters, the study will be implemented in full trimesters to avoid holiday times, including the assessments. Finally, the cycling skills will be assessed by the teacher using a checklist twice during the intervention, simulating real evaluation conditions. However, safety (e.g., to avoid risky activities where children perform skills that they have not learned yet) and time limitations (e.g., lack of more PE sessions to enlarge the intervention), will prevent the cycling skills assessment being carried out at baseline and follow-up, respectively. To summarize, doing research in schools is important to prevent unhealthy behaviours and related beliefs common in our society. Achieving a balance between the scientific requirements of randomized designs and the constraints imposed by real world circumstances is necessary to improve the quality of research conducted in educational settings [83]. It is also consistent with recent calls to achieve a balance between the established evidence-based pathway and a practice-based evidence pathway, and for a more nuanced approach to appraising the utility of diverse types of evidence [84].

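### The per-protocol sensitivity analysis can exclude pupils from the intervention arm only, and on some readings excludes those held out of session 3 for low skill, so it is likely to favour the intervention if commitment or skill relates to change

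*Protocol article*

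**What the plan says.** Section 6 (Data Analysis) states that "we will conduct a primary analysis based on an intention-to-treat principle" and then adds a per-protocol sensitivity analysis: "we will exclude participants who did not complete the intervention and/or did not reach a minimum of 75% of attendance". It does not define completion or the unit in which attendance is counted.

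Section 3.2 describes the intervention: "The 7 h intervention has four sessions", one of 60 minutes and three of 120 minutes. Section 7 lets teachers choose "spreading the 2 h lesson of the 2nd and 4th session in two 1 h sessions". Under section 4.2.2, pupils who miss the threshold on the session-2 skills checklist "will not be invited to participate in the next on-road cycling session", for safety reasons. The Abstract says that controls carry on as usual.

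Section 6 lists cycling skills among the mediators. Skills are scored only during intervention sessions 2 and 3, and section 7 explains why they cannot be assessed at baseline or follow-up.

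**The concern.** Completion and attendance are properties of the intervention arm alone. No parallel rule for controls is stated, and none could be built on skill, because controls are never scored. Followed as written, the analysis compares a selected group of intervention pupils with every control.

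The selection may go beyond ordinary absence. The trial itself keeps low-scoring pupils out of session 3. If those pupils count as non-completers, membership of the per-protocol set depends on cycling skill, which is a proposed mediator. It cannot be adjusted for, because it has no baseline value and no value in controls.

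At stake is the reading of the sensitivity analysis. A per-protocol effect larger than the intention-to-treat effect could be taken as support for the intervention when selection alone could produce it.

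**Working it through.** **1. Total dose (section 3.2).** Session lengths are 60, 120, 120 and 120 minutes. The sum is 420 min = 7 h, which reproduces the stated figure.

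**2. A pupil not invited to session 3 who attends everything else.**

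| Way of counting | Attendance | Against the 75% minimum |
|---|---|---|
| Sessions | 3/4 = 75.0% | met |
| Hours | (7 − 2)/7 = 5/7 = 71.4% | not met |
| Meetings, sessions 2 and 4 each split in two (six in all) | 5/6 = 83.3% | met |
| Completion read as all four sessions | not complete | not applicable |

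The unit matters for other pupils too. Missing only session 1 gives 75.0% of sessions but 6/7 = 85.7% of hours. Missing only session 2, or only session 4, gives 75.0% of sessions but 71.4% of hours.

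**3. The connective.** Suppose completion means all four sessions. Read as *or*, any missed session excludes, and the 75% minimum has no effect. Read as *and*, the pupil in step 2 stays in on a session count and is dropped on an hours count.

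**4. Illustration of selection in one arm.** Assume no true effect, a normally distributed trait (skill or commitment) with correlation ρ to the outcome, and removal of the lowest fraction f from the intervention arm only. That arm's mean rises by ρ·φ(z_f)/(1 − f) SD, where φ is the standard normal density and z_f its f-quantile. The documents give neither f nor ρ, so both are assumed.

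| f | ρ = 0.2 | ρ = 0.3 | ρ = 0.5 |
|---|---|---|---|
| 10% | 0.039 | 0.058 | 0.097 |
| 20% | 0.070 | 0.105 | 0.175 |
| 30% | 0.099 | 0.149 | 0.248 |

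For f = 20% and ρ = 0.3 there are 180 controls and 180 × 0.8 = 144 intervention pupils. The standard error is √(1/180 + 1/144) = 0.112 SD. A two-sided 5% test ignoring school clustering then rejects in about 15.6% of trials with no effect.

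**5. Limits of the illustration.** It describes an unadjusted comparison of post-intervention values. Section 6 also plans regression on post-minus-baseline change, with covariates that include bicycle ownership and home–school distance. If a stable trait relates equally to the baseline and post-intervention values, the bias in the change score is zero. What matters there is the trait's relation to change. For cycling to school, which the Introduction puts below 2%, a normal trait can correlate with the binary outcome by at most about φ(z)/√(p(1 − p)). At p = 0.02 this is 0.0484/0.14 = 0.35, so the ρ = 0.5 column is out of reach for that outcome.

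**The case against.** The case against has five parts.

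- **Completion need not mean all four sessions.** That reading makes the 75% minimum idle, which is a reason to doubt it. If completion means not dropping out and attendance is counted in sessions, the pupil held out of session 3 has exactly 75% and stays in. This stands. A reader might infer that the rule certainly removes low-skill pupils, or that its two criteria contradict each other. The text supports neither: two criteria joined by and/or need not pick the same pupils, and the outcome depends on the reading.
- **Definitions may sit in the full protocol or analysis plan.** This is fair for the unit and for the meaning of completion. It does not answer the one-arm exclusion, which follows from the stated rule under any definition.
- **Direction and size are assumed.** This stands. The documents give no failure rate for the skills check, no attendance rate and no relevant correlation. A reader might set the illustrative range against the odds ratio of 1.5 in section 2.3.3 and call the bias a given share of the target effect. The planned change-score and covariate-adjusted models do not support that.
- **The primary analysis is intention-to-treat.** This stands, and nothing in the article says that the per-protocol result can override it.
- **A complier-average effect has its own weakness.** It assumes that allocation has no effect on pupils classed as non-attenders. Some of them will attend one or two sessions, and whole classes train together. This stands, so the estimate should be added with its assumption stated and not offered as an assumption-free replacement.

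**Conclusion.** The point holds in a limited form. The per-protocol comparison breaks randomisation, because its exclusions can fall on one arm only. It is likely to favour the intervention if commitment or skill is positively related to change in the outcomes, which is plausible but undocumented.

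Under at least two readings (completion as all four sessions with *or*, or attendance in hours) it also drops pupils whom the trial itself held out of session 3. That selects on a mediator which is unmeasured in controls.

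The range of 0.04 to 0.25 SD is an illustration for an unadjusted post-intervention comparison with 10–30% excluded and correlations of 0.2–0.5. It is not an estimate for this trial. The harm is confined to how a sensitivity analysis is read. The stronger inference, that the trial's main result is biased, is not supported.

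**What to change.** 1. **Use one rule.** Replace the and/or wording with a single attendance criterion in one named unit, counted against the sessions or hours to which the pupil was invited. A pupil not invited to session 3 who attends the rest then has 3/3 sessions or 5/5 hours, 100% either way, and is not classed as non-compliant. The unit must still be named, since it changes the result for other absences.
2. **Add an estimate that keeps every randomised pupil.** Report a complier-average causal effect with allocation as instrument and a school-level standard error. If controls have no access to the sessions, it is the intention-to-treat effect divided by the proportion of the intervention arm meeting the attendance definition, so a null effect stays null. State the exclusion restriction. A low threshold, such as any attendance, makes it more credible, because partial attenders then count as treated.
3. **Label the naive per-protocol comparison descriptive**, and say that it does not confirm the intention-to-treat result.

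The cost is a change of wording and one more model, with no new data. The downside is a wider interval and one added assumption. Because the complier-average estimate rescales the intention-to-treat effect, it is not an independent check of it. The session-3 rule itself is not questioned.
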